### Primary outcome measure

Roland Disability Questionnaire for Sciatica (RDQ). This illness-specific 23-item functional assessment questionnaire is frequently used for low back pain and sciatica [23]. Scores range from 0 to 23, reflecting a simple unweighted sum of items endorsed by the respondent. High score reflects severe disabling pain. Recovery of pain is defined as improvement of 11 points or more from baseline [24]. This self-report measure of physical disability due to low back and leg pain has shown high level of internal consistency, construct validity, and responsiveness [24,25]. The RDQ is the main primary outcome measure in this trial.

### Secondary outcome measures

#### 1) Perceived recovery

An important secondary outcome measure is perceived recovery according to the 7-point Likert scale, ranging from "complete recovery" to "worse than ever". This outcome scale has been used in previous studies and appears to be valid and responsive to change [26,27]. "Complete recovery" and "almost complete recovery" are considered good results. Perceived recovery will be documented by the patient, surgeon and research nurse.

#### 2) Visual Analogue Scale (VAS) of leg pain and low back pain

This parameter will measure the experienced pain intensity in the leg and low back during the week before visiting the research nurse. Pain will be assessed on a horizontal 100 mm scale varying from 0 mm, "no pain", to 100 mm, "worst pain imaginable". Patients do not see the results of earlier assessments and will score the pain experienced at the visit. Reliability, validity and responsiveness of VAS have been shown [28].

#### 3) Macnab classification of surgical result

Patients will be evaluated by the surgeon and research nurse using the Macnab classification [29] ranging from "excellent no pain; no restriction of activity, "good; occasional back or leg pain of sufficient severity to interfere with the patient's ability to do his or her normal work, or to enjoy leisure activity", "fair; improved functional capacity, but handicapped by intermittent pain of sufficient severity to curtail or modify work or leisure activities", and "poor; no improvement or insufficient improvement to enable increase in activities; further operative intervention required".

#### 4) The Short-Form 36 (SF 36)

The SF 36 is a generic health status questionnaire, which can be easily filled out at home. It consist of 36 questions measuring health on 8 multi-item dimensions with a score ranging from 0 (unhealthy) to100 points (optimal health) covering physical functioning, physical restrictions, emotional restrictions, social functioning, somatic pain, general mental health, vitality, and general health perception. This questionnaire has been used frequently and is validated in studies on low back pain and surgery [30,31].

#### 5) The Karasek Job Content Questionnaire

The work perception of the patient will be assessed according a 5-point standardized scale according to the Karasek Job Content Questionnaire. This questionnaire is designed to measure psychological demands, decision latitude, social support, physical demands, and job insecurity [32].

#### 6) Hospital Anxiety Depression Scale (HADS)

This questionnaire consists of 7 questions concerning depression and anxiety. The score ranges from 0 to 21. A high score indicates more complaints: a score between 0 and 7 excludes depression and anxiety, a score between 8 and 10 suggests probable depression/anxiety, and a score between 11 and 21 indicates depression/anxiety [33].

#### 7) Utility measurements

The EuroQol (EQ-5D) measures 5 dimensions (mobility, self-care, daily activities, pain/discomfort, anxiety/depression), on a 3 point scale (no, some, or extreme problems). For each health state described by the patients, a utility score can be calculated that reflects society's valuation of that health state. The Dutch tariff for the EQ-5D will be used [34]. Similarly, SF-6D utilities will be calculated from the SF-36 profiles [35]. Whereas the EQ-5D and SF-6D provide society's assessment of the patients' health, the patients themselves will also assess their own health on VAS, ranging from 0.0 (as bad as death) to 1.0 (optimal health). Both the EQ-5D and the VAS will be reported in questionnaires filled out at home.

#### 8) Radiological examinations

Preoperatively, all patient will undergo dynamic radiographs, CT and MRI. The exact slip percentage and the slip angle will be measured on plain X-ray. The localisation of nerve root compression (lateral recess, parapedicular underneath pseudojoint, neuroforamen between pedicle or slipped disc, or combination) and the amount of nerve root compression will be quantified on MRI. We have developed the following grading scale based on the epidural fat reduction in the neuroforamen: 0–25% fat reduction (grade 1), 25–50% fat reduction (grade 2), 50–75% fat reduction (grade 3), and more than 75% fat reduction (grade 4). In addition, the diameter of the neuroforamen will be measured on sagittal CT reconstructions. During the follow-up, dynamic X-rays, CT and MRI will be repeated (table 2).

### Other outcome measures

#### 1) Costs

The direct medical costs of hospital admission (fixed costs per admission, and variable costs per admission day) and surgery (including personnel and implants) will be estimated in all participating hospitals for cost-analysis. Using cost diaries, the patients will register other medical care (including physiotherapy, visits to general practitioners and medical specialists, nursing care and medication) and non-medical costs (including out-of-pocket expenses, domestic help and absenteeism). Each diary will cover 3 months and the research nurse will go through the diary with the patient on every follow-up visit, throughout the study period of 2 years. Costs will be calculated using standard prices, including time and travel costs [36]. Absenteeism will be valued according to the friction cost method.

#### 2) Incidence of re-operations

In previous studies concerning spine surgery the incidence of re-operations has been used to assess outcome. Also in this study, we will assess the incidence of re-operation. Every surgical re-exploration in both groups will be considered as re-operation.

#### 3) Complications

Side effects or complications that are ascribed to the treatment are recorded by the patients, their treating physicians and the research nurses.

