**Methods/design:**

All patients (age between 18 and 70 years) with sciatica or neurogenic claudication lasting more than 3 months due to spondylolytic spondylolisthesis grade I or II, are eligible for inclusion. Patients will be randomly allocated to nerve root decompression according to Gill, either unilateral or bilateral, or pedicle screw fixation with interbody fusion. The main primary outcome measure is the functional assessment of the patient measured with the Roland Disability Questionnaire for Sciatica at 12 weeks and 2 years. Other primary outcome measures are perceived recovery and intensity of leg pain and low back pain. The secondary outcome measures include, incidence of re-operations, complications, serum creatine phosphokinase, quality of life, medical consumption, costs, absenteeism, work perception, depression and anxiety, and treatment preference. The study is a randomised prospective multicenter trial in which two surgical techniques are compared in a parallel group design. Patients and research nurse will not be blinded during the follow-up period of 2 years.

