Although most surgeons perform nerve root decompression with instrumented fusion in the treatment of spondylolytic spondylolisthesis, scientific proof justifying instrumented spondylodesis over simple decompression is lacking. The clinical results of instrumented and noninstrumented spondylodesis seem comparable with decompression according to Gill; 60 to 90% of the patients have good results [4,6,15-20]. The main arguments that favour intercorporal instrumented fusion are enlargement of the neuroforamen to relieve nerve root compression, and prevention of progressive slippage. Instrumented spondylodesis, on the other hand, constitutes major surgery with considerable blood loss, longer operation time, and significant complication rates which correlate with the extent of fusion [19,21,22].

Gill's procedure is a less invasive alternative technique to instrumented fusion. The operation time is shorter and the paraspinal muscle injury is less extensive. Patients may have less surgery-related low back pain and mobilise quickly, indicating short hospitalisation, fast recovery and early resumption to work. In addition, costs and complications related to instrumented surgery are avoided. However, secondary instrumented surgery might be necessary in patients with recurrent or persisting leg pain due to foraminal nerve root compression [14].

The controversy in the treatment of low grade spondylolytic spondylolisthesis justifies a randomised controlled trial comparing instrumented spondylodesis with nerve root decompression alone. The purpose of our study, the Sciatica-Gill trial, is to assess the clinical outcome and cost effectiveness of both surgical strategies on the short term (12 weeks) and long term (2 years). There will be a trade-off between persisting or recurrent leg pain in the Gill group and higher complication rates and costs in the spondylodesis group. Secondly, various subgroups of patients will be identified who may benefit primarily from one of the allocated surgical treatments.

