### Randomisation procedure

Patients will be randomly allocated to nerve root decompression according to Gill, either unilateral or bilateral, or instrumented spondylodesis. The patient, surgeon, physiotherapist and research nurse are not blinded for the allocated treatment. Randomisation lists are prepared for every participating hospital separately using variable sized blocks of randomly allocated treatments to patients, sequentially numbered in order of inclusion, to ensure near-equal distribution of patients over the two randomisations arms in the hospitals. The data manager, who is not involved in the selection and allocation of patients, will prepare coded, sealed envelopes containing the treatment allocation. During the first visit of the research nurse, the envelope will be opened in presence of the patient and appointments will be made for the hospital admission. Surgery will be performed within 6 weeks after randomisation. Eligible patients who have a strong preference for one of the allocated surgical techniques, and are not willing to be randomised but are consenting to participation in the study, will be followed as a separate cohort.

Patients, who are randomised for nerve root decompression according to Gill and have persisting leg pain on the first follow-up moment at 12 weeks, are offered secondary instrumented spondylodesis. These patients will be analysed in the Gill group conform the intent-to-treat principle.

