### Outcome assessment

Most symptomatic patients with spondylolytic spondylolisthesis report leg pain, low back pain and disability to perform normal daily activities. We will assess the below described validated outcome parameters. Patients will not be informed about their previous scores. Follow-up examination will take place at 6, 12, 26, 52, 104 and 260 weeks after randomisation. Additionally, at 3, 156 and 208 weeks after randomisation, questionnaires will be sent by mail (table 2).

**Table 2 T2:** Data collection and outcome measures.

***Time in weeks***	*X*	*0*	***3***	*6*	*12*	*26*	*52*	*104*	***156***	***208***	*260*
Preferred treatment of patient/surgeon/RN	v										
Neurological examination	v			v	v	v	V	v			v
Randomisation	v										
Operation		v									
Perceived recovery according to patient (Likert)	v		**v**	v	v	v	V	v	**v**	**v**	v
Perceived recovery according to surgeon/RN (Likert)				v	v	v	V	v			v
Macnab	v			v	v	v	V	v			v
HADS	v			v	v	v	V	v			v
Severity of complaints (VAS)	v	v	**v**	v	v	v	V	v	**v**	**v**	v
Roland Disability Questionnaire	v	v	**v**	v	v	v	V	v	**v**	**v**	v
Karasek	v			v	v	v	V	v	**v**	**v**	v
SF-36	v			v	v	v	V	v	**v**	**v**	v
EuroQol	v	v	**v**	v	v	v	V	v	**v**	**v**	v
Patient diary	v		**v**	v	v	v	V	v	**v**	**v**	v
CPK		v									
X-ray	v				v		V	v			v
MRI	v						V				
CT	v				v		V				
(Re)-operation			**v**	v	v	v	V	v	**v**	**v**	v
Complications		v			v		V	v			v

X is randomisation and 0 is operation. On week 3, 156, and 208 (bold columns), questionnaires will be sent by mail

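### Complications enter the data if unblinded people ascribe them to treatment, so the comparison of postoperative complications is open to differential ascertainment; Table 2 separately leaves weeks 6 and 26 blank

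*Protocol article*

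**What the plan says.** The protocol article gives the recording rule in one sentence, under Other outcome measures, 3) Complications: "Side effects or complications that are ascribed to the treatment are recorded". The sentence names patients, treating physicians and research nurses as those who record.

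On blinding, Randomisation procedure states: "The patient, surgeon, physiotherapist and research nurse are not blinded for the allocated treatment". The abstract repeats this for follow-up: "Patients and research nurse will not be blinded during the follow-up period of 2 years". Treating physicians as a group are not said to be blinded anywhere.

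The Background makes complications one side of the question the trial is meant to answer, and states the expected direction: "There will be a trade-off between persisting or recurrent leg pain in the Gill group and higher complication rates and costs in the spondylodesis group". The abstract lists complications among the secondary outcomes; the main text places them under Other outcome measures.

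On timing, Outcome assessment states: "Follow-up examination will take place at 6, 12, 26, 52, 104 and 260 weeks after randomisation". Aligned with its column headings, the complications row of Table 2 is marked at operation and at weeks 12, 52, 104 and 260. It is blank at the week 6 and 26 examinations and at the mailed contacts in weeks 3, 156 and 208.

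**The concern.** Two separate weaknesses meet in this outcome.

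The first is the entry condition. If an event is recorded once someone has ascribed it to the operation, the count in each arm is the true rate multiplied by the probability of ascription. That probability can differ between arms when the people judging know the allocation and the protocol itself expects implant surgery to do worse. A new back or leg complaint may be put down to the screws in one arm and to the underlying disease in the other. This can create an arm difference, enlarge one or hide one. An event that was never written down cannot be recovered at analysis.

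The second is the schedule. Patients are examined at weeks 6 and 26, yet no complications entry is planned there. Events from those intervals must be recalled at week 12 or week 52, and some will be forgotten. This affects both arms.

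At stake is a listed secondary outcome that the Background sets against persisting leg pain in weighing the two operations.

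**Working it through.** The article states no complication rate, so there is no figure of its own to reproduce. The check is a comparison of the text, followed by an illustration on assumed values.

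**1. Which events depend on attribution**

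| Type of event | Attribution needed? | Where stated |
|---|---|---|
| Dural tear, nerve root damage, blood loss, judgement of screw and graft placement | No | Intervention, (B), list of surgical findings |
| Re-operation | No; every re-exploration in either group counts | Other outcome measures, 2) |
| Other complications | Yes, on the natural reading | Other outcome measures, 3) |

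The exposed part is therefore postoperative complications that did not lead to re-operation.

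**2. Schedule**

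- Examinations after surgery: weeks 6, 12, 26, 52, 104, 260.
- Complications entries after surgery: weeks 12, 52, 104, 260.
- Examinations without an entry: weeks 6 and 26.
- Interval spanning the week 26 visit: 52 − 12 = 40 weeks without a scheduled entry.
- For contrast, (re)-operation is marked at every postoperative contact from week 3 onward.

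**3. Illustration of the attribution filter**

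Let the true rate p be the same in both arms, and let s be the probability that an event is ascribed and recorded. The recorded rate is p × s, so the apparent risk ratio (spondylodesis over Gill) is s_B / s_A, whatever p is. Assume s_B = 0.90 and vary s_A. Patients per arm follow the Sample size section: 110 × 0.9 = 99.

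The chance of a falsely significant excess after spondylodesis (two-sided 0.05, so nominally 2.5% in that direction) is

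Φ{[d − 1.96 √(2 p̄(1 − p̄)/99)] / √[(a(1 − a) + b(1 − b))/99]},

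where a and b are the recorded rates, d = b − a and p̄ is their mean.

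Example with p = 0.20 and s_A = 0.70: a = 0.14, b = 0.18, d = 0.04, p̄ = 0.16. The pooled standard error is 0.0521 and the unpooled one 0.0520. Then (0.04 − 1.96 × 0.0521)/0.0520 = −1.19, and Φ(−1.19) is about 11.6%.

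| s_A | Apparent risk ratio | p = 10% | p = 20% | p = 30% |
|---|---|---|---|---|
| 0.90 | 1.00 | 2.5% | 2.5% | 2.5% |
| 0.70 | 1.29 | 7.5% | 11.6% | 16.5% |
| 0.60 | 1.50 | 12.3% | 21.8% | 32.8% |
| 0.50 | 1.80 | 19.5% | 36.7% | 54.5% |

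Every value of p, s_A and s_B is an assumption. The table shows how the mechanism behaves; it does not estimate the bias in this trial.

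**The case against.** The strongest reply is that this is one sentence in a condensed article. It does not say that unascribed events are discarded, and the full protocol or case record form may hold a checklist and an attribution field. That stands as a limit. A reader might infer that complications are recorded only if ascribed and that all others are lost; the wording makes this the natural reading but does not state it. The criticism concerns the rule as written, not missing detail.

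Second, much of the safety information bypasses the filter. Intraoperative findings and re-operations need no attribution. Neurological examination, the Macnab classification and the cost diary are also scheduled at weeks 6 and 26. This stands and narrows the point. The diary, however, is described as a cost instrument, so it gives traces of medically attended events and not a complications record.

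Third, a reader might infer that the blank cells themselves produce differential ascertainment. The documents do not support this, because the schedule is the same in both arms. One unequal route is conceivable: patients in the Gill arm with persisting leg pain are offered a second, instrumented operation at week 12, and its early postoperative period could fall in the 40-week interval. Week 52 still asks about complications, however, and the re-operation itself is captured.

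Fourth, many surgical complications leave little room for judgement about cause, so large attribution gaps across all events are speculative. Even the 70% against 90% example gives an expected z of only 0.04/0.0520 = 0.77 at a true rate of 20%. This stands, and it is why no size is claimed.

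Finally, a reader might call this the trial's key safety comparison. The article does not. It ranks complications as a secondary or other outcome, although the Background gives them weight in the trade-off.

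**Conclusion.** The point holds in limited form. As written, the rule makes ascription by people who know the arm the gateway to the complications data, and the protocol announces in advance which arm it expects to do worse. The comparison of postoperative complications that are neither re-operations nor intraoperative findings is open to differential ascertainment. The blank cells at weeks 6 and 26 are a second and separate fault: under-recording and recall in both arms, with 40 weeks lacking a scheduled entry.

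The size is unknown. The apparent risk ratios of 1.29 to 1.80 rest wholly on assumed recording probabilities. The real gap could be negligible, or could run the other way and hide a difference. The conclusion rests on reading the Complications sentence in its natural sense; a full protocol that already records events regardless of cause would remove the first fault. The primary outcome is not affected. The change should be made, since it is cheap and lost events cannot be restored later.

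**What to change.** 1. Reword the Complications paragraph so that all complications and adverse events are recorded in both arms from the same fixed list, whatever the presumed cause.
2. Record attribution to the operation as a separate field, so that it describes an event and does not decide whether it is entered.
3. Add complications entries at weeks 6 and 26 to Table 2, so that every existing visit has one.
4. State that arms are compared on all events first and on attributed events second.

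The cost is a few more form items and some data entry at visits that already take place. Blinding of the surgery is not required. The all-event comparison will include some events unrelated to surgery, which may dilute a true difference; the second comparison, on attributed events, covers that.

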#### 4) Serum creatine phosphokinase (CPK)

Creatine phosphokinase is a known marker of muscle damage. Previous study has demonstrated a dose-response relation between the extend of surgery and CPK values [37]. Therefore, we will determine the serum CPK before surgery and 1 day after surgery in both groups. Whether CPK is correlated with postoperative low back pain and clinical outcome will be determined as well.

### Sample size

The sample size is calculated on the basis of the RDQ both at both short term and long term follow-up. A difference in effectiveness is considered clinically relevant whenever patients with nerve root decompression alone will obtain at least 20% difference in RDQ score. Instrumented spondylodesis is assumed to result in at least 60% good outcome at 12 weeks. This means that 80% of the patients treated with nerve root decompression alone should have good results in order to proof superiority of Gill's procedure. Treatment is considered to be justified in case of improvement of at least 7 points on the RDQ score; 20% difference corresponds to 8.4 points improvement on in the RDQ score. With a power of 90% and a two-tailed significance level of 0.05, 220 patients with symptomatic spondylolytic spondylolisthesis grade I and II are needed (110 patients in both treatment groups, including 10% loss to follow-up). The numbers used for this sample size calculation are retrieved from the 1 and 5-years results of the Maine Lumbar Spine Study [38,39].

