## Methods/design

We designed a multicenter randomised controlled cost-effectiveness trial on the treatment of low-grade spondylolytic spondylolisthesis in which two surgical techniques are compared in a parallel group design. The primary outcome measure is the Roland Disability Questionnaire (RDQ) for sciatica. The follow-up period will last 2 years (with extension to 5 years). In order to collect enough patients, a multicenter design is necessary. The study protocol is approved in all participating hospitals by the Medical Ethics Committee.

We hypothesise that nerve root decompression according to Gill is more (cost-)effective on the short term (12 weeks) and equally (cost-)effective on the long term (2 years). Equal effectiveness is defined as maximal 4 points difference on the RDQ score between decompression and instrumented fusion. Moreover, we will identify subgroup of patients who may benefit more of one of the allocated treatments.

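### The sample size is said to cover short and long term, but only 12-week superiority is calculated; with the stated 10% loss that gives about 87% power, and power for 2-year equality is not shown

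*Protocol article*

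**What the plan says.** The Methods/design section states a two-part hypothesis: Gill's procedure is expected to be more effective at 12 weeks and equally effective at 2 years. It also fixes what equality means: "Equal effectiveness is defined as maximal 4 points difference on the RDQ score between decompression and instrumented fusion".

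The Sample size section opens with "The sample size is calculated on the basis of the RDQ both at both short term and long term follow-up". The inputs that follow are:

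- "Instrumented spondylodesis is assumed to result in at least 60% good outcome at 12 weeks".
- For superiority of Gill's procedure, "80% of the patients treated with nerve root decompression alone should have good results".
- A translation into RDQ points, from a minimum worthwhile improvement of 7 points: "20% difference corresponds to 8.4 points improvement on in the RDQ score". No standard deviation is attached.
- "With a power of 90% and a two-tailed significance level of 0.05, 220 patients", as 110 per group with 10% loss to follow-up included.
- The numbers used "are retrieved from the 1 and 5-years results" of an external lumbar spine study.

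The section gives no 2-year rate, no standard deviation and no equivalence or non-inferiority calculation. The 4-point margin does not appear in it.

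**The concern.** The opening sentence claims a calculation for two time points, but every worked input belongs to one of them. The two parts of the hypothesis are also different kinds of claim. Power to show a 20-point difference in good outcome at 12 weeks says nothing direct about power to show that mean RDQ scores lie within 4 points at 2 years.

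A reader will attach the single printed 90% to both claims. If the 2-year confidence interval then crosses the margin, the result may be read as a failure in a trial known to have had 90% power for it, although the document does not establish that. Separately, the printed 90% needs checking for the 12-week claim itself, because the patient number is said to include the loss to follow-up.

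**Working it through.** **Inputs.** From the Sample size section: p1 = 0.60, p2 = 0.80, two-sided alpha 0.05 (z = 1.960), power 90% (z = 1.282), 110 per arm including 10% loss. Evaluable per arm: 110 × 0.90 = 99. From Methods/design: equality margin 4 RDQ points. Assumed, because the document gives none: the standard deviation (SD) of the RDQ at 2 years.

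**1. The plan's own figure.** Normal test for two proportions with pooled variance, mean proportion 0.70:

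n = [1.960 × √(2 × 0.70 × 0.30) + 1.282 × √(0.60 × 0.40 + 0.80 × 0.20)]² / 0.20²

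= (1.270 + 0.811)² / 0.04 ≈ 108.2, so 109 evaluable per arm (218 in total).

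With 10% loss: 109 / 0.90 = 121.1, so 122 per arm (244 in total). Other common two-sided formulas also exceed 220 once loss is added:

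| Method | Evaluable per arm | With 10% loss | Total |
|---|---|---|---|
| Unpooled | 106 | 118 | 236 |
| Arcsine | 108 | 120 | 240 |
| Pooled | 109 | 122 | 244 |
| Continuity-corrected | 119 | 133 | 266 |

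The printed 220 is close to the pooled 218 before any loss. A one-sided, continuity-corrected calculation gives 98, then 109 with loss (218 in total), but the text says two-tailed.

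**2. Power at 12 weeks.** Power = Φ[(0.20 × √n − 1.270) / 0.632].

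- n = 99: (1.990 − 1.270) / 0.632 = 1.138, power 87.2%.
- n = 110: (2.098 − 1.270) / 0.632 = 1.308, power 90.5%.

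**3. Power for 2-year equality.** Equality is taken as shown when the 95% confidence interval lies within ±4 points, with no true difference and 99 per arm. SE = SD × √(2/99) = 0.1421 × SD. Power = 2Φ(4/SE − 1.96) − 1.

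| Assumed SD | SE | 4/SE − 1.96 | Power |
|---|---|---|---|
| 6 | 0.853 | 2.730 | 99.4% |
| 7 | 0.995 | 2.060 | 96.1% |
| 8 | 1.137 | 1.558 | 88.1% |
| 9 | 1.279 | 1.167 | 75.7% |
| 10 | 1.421 | 0.854 | 60.7% |

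Power stays at or above 90% up to SD = 4 / [(1.960 + 1.645) × 0.1421] ≈ 7.8. Any true difference lowers these figures.

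**4. Both parts together.** The probability that two events both occur cannot exceed the probability of either one. Whatever the 2-year SD and the correlation between the two results, power for both parts is at most the 12-week power: 87.2% at 99 evaluable per arm.

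**The case against.** The strongest reply is that a journal article condenses its protocol and may print only the calculation that drives the size. With no true difference, 2-year equality at 90% power needs about 41, 59, 80 and 104 evaluable per arm at SDs of 5, 6, 7 and 8. All are below the 109 needed at 12 weeks, so the opening sentence may even be true. This stands, and it rules out an inference that a reader might draw: that the trial is underpowered at 2 years, or that the printed 90% fails because the hypothesis has two parts. The missing calculation shows neither.

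Three related limits also stand:

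- The 20-percentage-point difference is the plan's criterion for superiority, not its margin for equality, so it should not be used to judge the 2-year claim.
- The document sets no rule that the trial succeeds only if both parts do, and multiplying the two powers would assume independence between repeated scores in the same patients. Only the upper bound is safe.
- A reader might infer that the 60% rate itself was observed at 1 or 5 years. The text says only that the numbers came from those results, not which number came from where.

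It can also be said that the assumption is at least 60%, and that a higher rate with the same 20-point gap raises power: at 99 per arm, 65% versus 85% gives 90.7% and 70% versus 90% gives 94.6%. That is correct, but the calculation as printed is for 60% versus 80%, and the 90% is attached to those figures.

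Condensation does not answer the loss arithmetic, because all its inputs are printed.

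**Conclusion.** The point holds in a limited form. The article claims a size calculated for both time points and shows one for 12-week superiority only. Power for 2-year equality within 4 RDQ points is undocumented. It could be comfortably above 90% or well below it, depending on an SD that the article does not give and on the true difference.

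The shortfall that can be demonstrated is at 12 weeks: about 87% with the 99 evaluable patients per arm that the plan expects, and 90% only if essentially all 110 are evaluable. This rests on the printed rates, two-sided 0.05 and the usual pooled normal test. It is a gap of about three percentage points, and it caps the power for the whole hypothesis at the same 87%.

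**What to change.** Keep 220 patients and revise the Sample size section as follows:

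1. State that the printed power refers to the 12-week superiority comparison only, and restate it as about 87% at 99 evaluable per arm (90% only if all 110 are evaluable).
2. Give the power for 2-year equality on the 4-point margin at 99 evaluable per arm, with the assumed SD and its source. If the SD is uncertain, show a range such as the one tabulated above. Otherwise, remove the claim that the size was calculated for long-term follow-up.

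The cost is a few sentences and one calculation. The stated power becomes slightly less favourable, and no extra patients are needed.
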